#### **6.1.2 Secondary study parameters/endpoints**

Secondary outcomes are: ADL functionality (KATZ), Balance test (SPPB), Tendency to Fall (FES-I), Numbers of falls, additional injuries as a result of falling, Pain (NRS), Re-interventions, Mobility (pre-fracture mobility score), Discharge destination, (surgical) complications and cost-effectiveness.

### **6.2 Randomisation, blinding and treatment allocation**

Eligible patients admitted to the hospitals where both surgical techniques are practiced, are invited for participating in our RCT prior to the surgery. When patients agree to participate, written informed consent will be obtained and patients will be randomised between the PLA and the DLA. Randomisation will be stratified per center and per orthopaedic/trauma surgeon. Randomisation will be done in CASTOR EDC, a secured study and data management system with built-in randomisation (variable block method).

Surgeons, patients or outcome assessors cannot be blinded since the different surgical approaches are easily distinguishable (i.e. based on the location of the scar).

### 6.3 Natural Experiment

Alongside the RCT we will conduct a natural experiment in hospitals with surgeons who are only comfortable (or competent) in performing one of the two surgical approaches. Allocation to treatment using the PLA or DLA is determined by the hospital where the patient is admitted to (i.e. by the topographical location where the trauma takes place). These natural factors are outside the control of the investigators, resembling random assignment. Patients in the natural experiment are invited for participating after surgery, and informed consent will be obtained for follow-up and data usage.

We will recruit participating centers based on surgical expertise balancing number of centers based on surgical approaches used.

Although we are aware this is not a formal randomization on participant level, the NE design has several advantages(22):

- Most importantly, we will prevent surgical expertise bias.
- The NE design will facilitate better generalizability of our trial results since more centers are able to participate. Generalizability will help implementing our trials results.
- We will be able to reduce selection bias, by including patients and surgeons who may not have agreed to randomisation.

Interventions to prevent other forms of bias:

- Selection bias: We will be able to compare the RCT and NE results with anonymous data from the DHFA registry that includes all patients who were treated for hip fractures in the participating centers.
- Detection bias: Patients participating in our study will be blinded to the study hypothesis.
- Attrition bias: Follow-up will be performed by a research coordinator assuring completeness of data.
- Reporting bias: We will publish our study protocol in an open access peer reviewed journal and at [www.clinicaltrials.gov](http://www.clinicaltrials.gov)
- Performance bias: The Dutch Hip Fracture Guideline introduced in 2015 will prevent performance bias since treatment protocols are standardised apart from the surgical approach used. Hip fracture guideline adherence is good (23).

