#### 4.2 Inclusion criteria

In order to be eligible to participate in this study, a subject must meet all of the following criteria:

- $\geq 18$  years at time of trauma
- Acute hip fracture
- Hemiarthroplasty as recommended treatment according the national guidelines
- Dutch or English fluency and literacy
- Informed consent or by proxy in patients with mental impairment

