#### 4.4 Sample size calculation

We based our sample size calculation on a superiority design. As stated before the EQ-5D will serve as primary outcome measure. We have used the results from earlier studies on this subject for our sample size calculation(17–19). For the sample size calculation, we hypothesized that the EQ-5D will be higher in the PLA group. Using a two-sided significance level ( $\alpha$ ) of 0.05 and a power ( $\beta$ ) of 80% with a standard deviation (SD) of 0.3 and a minimal clinical important difference (MCID) of 0.08 (derived from the study mentioned before) a total of 222 subjects are needed in each treatment arm. Taking into account a 25% loss to follow-up after six months, a total number of 610 participants are needed in this superiority design.

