#### *Technique classic PLA*

Patient in side position. Exposure is made through a 10-15 cm curved incision that begins about 7 cm cranial and posterior of the greater trochanter and continue across the greater trochanter down towards the femur shaft. In line with the skin incision, the fascia lata is incised to exposure the distal vastus lateralis. The gluteus maximus muscle is separated by blunt dissection. Stretch the short external rotators and detach the piriformis and obturator internus muscle. Expose the hip joint by a longitudinally incision of the posterior capsule. Dislocate the hip with internal rotation after capsulotomy.(20)

[figure not shown]

The type and brand of the prosthesis will be left to the surgeons' discretion. Hospital protocols and guidelines will be followed regarding physical therapy and rehabilitation program and will be recorded.

Patients allocated to the DLA group will be treated with a cemented hemiarthroplasty using the DLA.

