**8.1 Primary study parameter(s)**

In the primary GEE model, the primary outcome variable studied (health related quality of life on EQ-5D) will be analyzed as a dependent variable, using treatment allocation (DLA vs. PLA) as between subjects' variable and time as within subjects' variable. In a similar way, continuous secondary outcome variables will be analyzed using similar GEE models. All models will assess the interaction term of group and time, to evaluate whether the change over time differed between PLA and DLA.

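### In the natural experiment the approach is nested in hospital, yet the protocol likens this to randomisation, and its only effectiveness model has no hospital level and no stated cohort

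*Protocol*

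**What the plan says.** - **Allocation in the NE.** Section 6.3 places the NE in hospitals whose surgeons perform only one of the two approaches, so the admitting hospital decides which approach a patient gets. It then says: "These natural factors are outside the control of the investigators, resembling random assignment". The same section concedes that this is not formal randomisation of participants.
- **Entry.** "Patients in the natural experiment are invited for participating after surgery, and informed consent will be obtained for follow-up and data usage". RCT patients, by contrast, are invited before surgery (6.2).
- **Local practice.** Under the PLA technique in 5.1: "Hospital protocols and guidelines will be followed regarding physical therapy and rehabilitation program and will be recorded". The DLA text says the same of each centre's rehabilitation. Both leave the type and brand of prosthesis to the surgeon. Section 6.4 (Surgery) leaves antibiotic and thromboembolic prophylaxis and wound dressing to the surgeon and local guidelines. Section 6.3 nevertheless states that the national guideline will prevent performance bias because treatment is standardised apart from the approach.
- **Effectiveness model.** Section 8.1 specifies a GEE for EQ-5D "using treatment allocation (DLA vs. PLA) as between subjects' variable and time as within subjects' variable", plus the group-by-time interaction. No hospital term, covariate or cohort is named.
- **Clustering.** Section 8.3 plans multilevel models for the economic evaluation, and warns that ignoring clustering, for example by hospital, can distort both uncertainty and point estimates.
- **Size.** Section 4.4: "a total number of 610 participants are needed in this superiority design". It does not say whether NE patients count towards this number.

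**The concern.** When each hospital uses one approach, the unit that is allocated is the hospital. Any hospital-level difference that affects EQ-5D at six months becomes part of the PLA-DLA contrast. Patients from one hospital also do not supply independent information on that contrast. A model with the patient as the only unit ignores both facts.

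Two things are at stake. First, a separate NE result from this model would look more precise than it is and could be biased. Second, if NE patients were pooled into the primary model or counted towards the 610, the randomised comparison would be diluted with non-randomised data and would have fewer randomised patients than planned.

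**Working it through.** **1. The plan's own sample size.** Inputs from section 4.4: two-sided alpha 0.05, power 80%, SD 0.3, difference 0.08, loss 25%.

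- n per arm = 2 × (1.96 + 0.84)² × 0.3² / 0.08² = 221 with unrounded normal quantiles. The t-test version gives 221.7, i.e. the stated 222.
- 2 × 222 = 444, and 444 / 0.75 = 592. The stated 610 is 18 higher, about 3%.

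The figure reproduces closely. It assumes independent patients, that is, a design effect of 1. That fits an RCT randomised within centre and surgeon, but not an NE allocated by hospital.

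**2. The statements set side by side.** Section 6.3 relies on standardised care to rule out performance bias. Sections 5.1 and 6.4 leave prosthesis, rehabilitation, prophylaxis and wound dressing to surgeon or centre. In the RCT, stratifying by centre and surgeon (6.2) balances these factors. In the NE nothing does, because each hospital contributes to one approach only. The bias measures listed in 6.3 include a comparison with anonymous DHFA data but neither an adjusted nor a cluster-aware analysis.

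**3. Effect on the test, as an illustration.** The protocol gives no hospital ICC, number of NE hospitals or NE patients per hospital. Assume m = 20 to 60 patients per hospital and ICC = 0.01 to 0.05.

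- Design effect: DE = 1 + (m − 1) × ICC
- True SE / reported SE = √DE
- Actual type I error of a nominal 5% patient-level test of levels = 2 × [1 − Φ(1.96 / √DE)]

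| m | ICC | DE | SE ratio | Type I error |
|---|---|---|---|---|
| 20 | 0.01 | 1.19 | 1.09 | 7.2% |
| 20 | 0.05 | 1.95 | 1.40 | 16.0% |
| 40 | 0.02 | 1.78 | 1.33 | 14.2% |
| 40 | 0.05 | 2.95 | 1.72 | 25.4% |
| 60 | 0.01 | 1.59 | 1.26 | 12.0% |
| 60 | 0.05 | 3.95 | 1.99 | 32.4% |

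A simulation with a hospital random effect, 4 hospitals per approach and 30 patients each, gave 8.8%, 12.0% and 21.1% at ICC 0.01, 0.02 and 0.05. The formula gives 8.4%, 11.9% and 21.1% for the same settings.

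**4. Precision that more patients cannot buy.** The hospital SD is 0.3 × √ICC, i.e. 0.030 to 0.067 for ICC 0.01 to 0.05. With an assumed k = 4 hospitals per approach, hospital variation alone gives the difference an SE of hospital SD × √(2/k) = 0.021 to 0.047. That is 27% to 59% of the 0.08 difference in section 4.4. Adding patients within hospitals does not reduce it.

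**5. Limit of the illustration.** Steps 3 and 4 concern levels at one time point. Section 8.1 tests group by time, where stable hospital differences cancel. Differences that arise after surgery, such as centre-specific rehabilitation, do not cancel. The relevant ICC is then that of change, which may be smaller.

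**The case against.** The strongest reply is that section 8 never mentions the NE. Its GEE is introduced on an intention-to-treat and per-protocol basis, and section 6.7 ties intention-to-treat to patients who leave their randomised treatment. The model may therefore be meant for the RCT, with the NE model left to an SAP. The phrase in section 8 about patients treated with PLA or DLA belongs to the descriptive baseline comparison, so it does not extend the GEE to the NE. Section 6.3 places the NE alongside the RCT and speaks of the results of each, which leans against pooling. It also concedes that participants are not formally randomised. Section 6.9 collects age, gender, ASA, BMI, cognitive impairment and date of death for all consecutive patients, so selection into the NE can be examined.

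Much of this stands. A reader might infer that the plan pools the NE into the primary test, or that the primary result is already compromised. The documents support neither: pooling is not stated, and randomisation within centre and surgeon keeps the RCT free of confounding by hospital.

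Three things survive. Section 6.4 restricts only the SPPB to the RCT, so EQ-5D follow-up covers the NE, and the only effectiveness model given for it names no cohort. The registry data can show who was missed, but no adjustment of the PLA-DLA contrast is planned from them. The two statements in 6.3 conflict with the protocol's own text, whatever an SAP may add.

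**Conclusion.** The point holds in conditional form. In the NE, approach is nested in hospital and mixed with local care, and entry after surgery adds possible selection. The likeness to random assignment and the claim that performance bias is prevented are therefore not supported by the protocol itself.

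If the section 8 model is used for the NE, or for RCT and NE pooled, its standard errors are too small for any hospital ICC above 0 in the contrast tested, and its estimate can be confounded. The 7% to 32% rejection rate describes an NE-only comparison of levels. It rests on an assumed ICC and hospital size and would be smaller for group by time to the extent that hospital differences are stable. It describes neither the RCT nor a mixed sample. Confounding comes on top, has no size that the protocol allows one to compute, and does not shrink with more patients per hospital.

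**What to change.** 1. In sections 4.4 and 8, state that the 610 and the primary test refer to randomised patients only.
2. In section 8, add a separate NE analysis, reported as observational and supportive. Use hospital as a random effect (the multilevel approach of 8.3) with inference suited to few hospitals. A hospital fixed effect cannot be used in the NE alone, because each hospital has one approach.
3. Adjust the NE analysis for pre-specified patient-level baseline factors that are already collected, for example age, sex, ASA, cognitive impairment, living status, KATZ, pre-fracture mobility and baseline EQ-5D.
4. In section 6.3, replace the likeness to random assignment and the claim about performance bias with a statement that the NE is observational and that local care varies with hospital.

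This costs protocol and SAP wording and needs no new data. The downside is wider NE intervals, which reflect the number of hospitals and not only the number of patients. Adjustment will not remove unmeasured hospital differences.

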## 6.4 Study procedures

|                              | Screening                              | Informed consent procedure       | Baseline assessment | Surgery                                               | 4 weeks follow up              | 3 months follow up                                                              | 6 months follow up                                                              |
|------------------------------|-----------------------------------------------|-----------------------------------------|----------------------------|--------------------------------------------------------------|---------------------------------------|----------------------------------------------------------------------------------------|----------------------------------------------------------------------------------------|
| Clinician/ researcher | Identify eligible patients with hip fractures | Explain PIF, answer questions, sign ICF | DHFA*                      | Record implant details
Record complications               |                                       | Standard clinical follow up, including DHFA                                            | Standard clinical follow up                                                            |
| Researcher            | Identify eligible patients with hip fractures | Answer additional questions if needed   | - DHFA
- EQ-5D          | Screen surgical report for relevant information if necessary | Health care utilization questionnaire | - EQ-5D
- FES-1 scale
- NRS
- SPPB
- Health care utilization questionnaire | - EQ-5D
- FES-1 scale
- NRS
- DHFA
- Health care utilization questionnaire |
| Patient/ proxy        |                                               | Read PIF, ask questions, sign IC        | Complete questionnaire     |                                                              | Complete questionnaire                | - Complete questionnaires
- SPPB at outpatient clinic                               | Complete questionnaires                                                                |

\*DHFA is a registry used in standard care includes: living status, pre-mobility score, KATZ, ASA, complications, discharge destination, re-operations

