When hospitals are participating with this trial, treating physicians will be asked to screen if patients admitted to the hospital with a hip fracture are eligible for study entry. If inclusion criteria are met, they can contact the research coordinator by phone (☎ ([contact]) or visit the trial website, for further assistance with obtaining informed consent, randomisation and inclusion of the patient.

To obtain informed consent, the patient information letter will be handed out to eligible patients or to their health care proxy. Hard copies will be available in all participating hospitals or could be found as a download on the trials' website.

Hip fractures are injuries where treatment is required in less than 48 hours for optimal outcomes. Therefore, the time in which patients can consider if they are willing to participate to the study, is limited to the time until surgery. Informed consent of patients in the Natural Experiment can be obtained after surgery. The research coordinator will contact these patients.

For patients with severe cognitive impairment due to dementia, informed consent will be obtained by their health care proxy. It is to the doctors' opinion to determine if a patient

has a cognitive impairment. When the diagnosis is not clear, a clinical geriatric doctor will be consulted

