## 6.9 Missing subjects

Subject can be missed during screening for study entry and subjects can refuse to participate in the study. Whether there are differences in baseline characteristics between the missing subjects and included subjects, data from the DHFA registration is collected. Of all consecutive patients treated with a hemiarthroplasty after femoral neck fracture admitted in one of the participating hospitals during the inclusion period, the following variables will be collected: age, gender, ASA, BMI, cognitive impairment and date of death.

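### Natural-experiment patients enter after surgery with no fixed window, so early deaths and severe complications in patients who never enrol can be missed there but not in the RCT, and the planned registry checks only partly cover this

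*Protocol*

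**What the plan says.** **Entry to the RCT.** Under Protocol section 6.2, eligible patients in hospitals that practise both techniques "are invited for participating in our RCT prior to the surgery". Consent and randomisation follow, still before the operation.

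**Entry to the natural experiment.** Section 6.3 states: "Patients in the natural experiment are invited for participating after surgery, and informed consent will be obtained for follow-up and data usage". Section 6.4 repeats this: "Informed consent of patients in the Natural Experiment can be obtained after surgery. The research coordinator will contact these patients". Neither section gives a time by which contact must be made. Proxy consent is provided for: "For patients with severe cognitive impairment due to dementia, informed consent will be obtained by their health care proxy". Sections 9.2 and 9.3 extend it to incapacitated subjects, with dementia as the example. No route is described for a patient who dies before contact.

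**Check in section 6.9.** Its stated purpose is: "Whether there are differences in baseline characteristics between the missing subjects and included subjects, data from the DHFA registration is collected". The population is defined as "Of all consecutive patients treated with a hemiarthroplasty after femoral neck fracture admitted in one of the participating hospitals during the inclusion period", and for these patients "the following variables will be collected: age, gender, ASA, BMI, cognitive impairment and date of death".

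**Check in section 6.3.** Under selection bias, the protocol says it will be possible to compare RCT and natural-experiment results with anonymous DHFA data on all hip-fracture patients treated in the participating centres. No variables and no split by approach are named.

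**What the DHFA holds.** The footnote to the schedule in section 6.4 lists "living status, pre-mobility score, KATZ, ASA, complications, discharge destination, re-operations".

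**Outcomes affected.** Section 6.1.2 names re-interventions, complications and discharge destination among the secondary outcomes.

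**The concern.** In the RCT the denominator is fixed before the operation, so an early death or complication counts against the approach to which the patient was allocated. In the natural experiment the denominator consists of patients who survived long enough to be contacted, could be approached directly or through a proxy, and agreed. All of that happens after the exposure, and approach or hospital may influence it. Adjusting enrolled patients for case mix cannot repair this, because the patients who are lost are not in the data to be adjusted.

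Approach in the natural experiment is fixed by hospital (section 6.3). Any difference between hospitals in how soon or how persistently patients are contacted would therefore feed into the comparison of the posterolateral approach (PLA) with the direct lateral approach (DLA). Rates in the two cohorts could also differ only because entry is timed differently.

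Section 6.3 presents the natural experiment as reducing selection bias, by admitting patients and surgeons who would not accept randomisation. It does not discuss selection that arises after surgery. What is at stake is the comparison of early harm between approaches in that cohort.

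**Working it through.** **1. The passages side by side**

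| Item | RCT | Natural experiment |
|---|---|---|
| Time of invitation | Before surgery (6.2) | After surgery, no window (6.3, 6.4) |
| Patient dies before contact | Does not arise: already enrolled | No route to entry described |
| Early complication, patient later enrolled | Recorded | Recoverable from the DHFA and the surgical report (6.4) |
| Early complication, patient never enrolled | Does not arise | Not in the study data |

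The loss is confined to natural-experiment patients who never enrol.

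**2. What the section 6.9 extract can show**

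| Variable | In the 6.9 list | In the listed DHFA items (6.4) |
|---|---|---|
| Date of death | Yes | Not listed, but 6.9 says it is collected |
| Complications | No | Yes |
| Re-operations | No | Yes |
| Discharge destination | No | Yes |
| KATZ | No | Yes |
| Mobility | No | Yes |
| Living status | No | Yes |
| Hospital or approach | No | Not listed |

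Excess early death among non-enrolled patients could be seen if it were analysed, but the stated comparison is of baseline characteristics. As that comparison is not split by approach, opposite selection in PLA and DLA hospitals could cancel.

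**3. Illustration of size**

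The protocol gives no early-event rates and no enrolment probabilities, so it has no figure of its own to reproduce here. Everything in this step is assumed.

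Let *r* be the true early-event risk and *k* the chance of enrolment after an event relative to that without one. The risk seen among enrolled patients is

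observed risk = *rk* / (*rk* + 1 − *r*)

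Assume *r* = 0.06 for PLA and 0.03 for DLA, a true difference of 3.0 points, with the same *k* in both:

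| *k* | PLA | DLA | Difference (points) |
|---|---|---|---|
| 0.25 | 0.015/0.955 = 1.57% | 0.0075/0.9775 = 0.77% | 0.80 |
| 0.50 | 0.030/0.970 = 3.09% | 0.015/0.985 = 1.52% | 1.57 |
| 0.75 | 0.045/0.985 = 4.57% | 0.0225/0.9925 = 2.27% | 2.30 |
| 1.00 | 6.00% | 3.00% | 3.00 (no bias) |

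If instead the true risk is 6% with both approaches, but *k* is 0.9 in one group of hospitals and 0.5 in the other, the observed risks are 0.054/0.994 = 5.43% and 0.030/0.970 = 3.09%. A difference of 2.34 points appears where none exists, and its sign depends on which hospitals have the lower *k*. The mechanism can therefore shrink a difference or create one.

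**The case against.** **The planned checks could reveal the loss.** Much of this stands. Death is the clearest event that prevents enrolment, and section 6.9 collects its date for all consecutive patients. Section 6.3 offers a second comparison, of results this time, with a registry that holds complications and re-operations, and in natural-experiment hospitals approach follows from hospital. A reader might infer that the plan records no early events outside the consenting patients, or that its checks cannot detect the problem. The documents do not support that. What remains is that 6.9 states only a pooled baseline comparison, that 6.3 names neither variables nor a split by approach, and that its data are anonymous with no statement that hospital is kept.

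**Under-counting is not certain.** This is correct. Complications before consent are recoverable in anyone who later enrols, proxies can consent for incapacitated patients, and nothing says how many patients are missed.

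**The direction is unsupported.** This also stands. The harm that the introduction expects from PLA is dislocation, and nothing suggests that a dislocation stops a patient being reached or consenting. A reader might infer that the cost of PLA is necessarily understated; the protocol gives no basis for that. Nor does it give a reason for enrolment to differ between hospital groups.

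**The reach is limited, and splitting tables is work for a statistical analysis plan.** The primary outcome is the EQ-5D-5L at six months, which needs a living patient in either cohort, and the RCT comparison is untouched. The split alone could wait for an analysis plan. The variable list could not: section 6.9 fixes what is extracted, and fields not extracted cannot be analysed later.

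**Conclusion.** The point holds as a gap in the natural experiment's handling of early harm. Entry there depends on being reached and consenting after surgery, with no window, whereas RCT entry precedes surgery. Early deaths and severe early complications in patients who never enrol can therefore be missed in one cohort only. The registry checks are incomplete, not absent.

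The size and direction of any bias are unknown. The shrinkage from 3.0 points to between 0.8 and 2.3 points rests on assumed risks of 6% and 3% and on assumed relative enrolment of 0.25 to 0.75, equal in both approaches. If patients with early events enrol as readily as others, there is no bias. The consequence falls on secondary outcomes in the non-randomised cohort, and the correction is a worthwhile, low-cost improvement.

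**What to change.** 1. In section 6.9, add complications, re-operations, discharge destination, KATZ, mobility and living status to the registry extract, together with the hospital or approach field.
2. Run the comparison of included and missing subjects by approach, and separately for RCT and natural-experiment centres.
3. As a supporting analysis for the natural experiment, compare death, complications, re-operations and discharge destination by approach, counted from the day of surgery. Use all consecutive hemiarthroplasty patients of those centres, not only those who consented.

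**Cost.** An all-patient extract is already planned, so this means more fields and a few more tables. No visit, treatment or sample-size change follows. There are three limits:

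- For non-participants, only anonymous registry-level detail is available.
- Injury severity score, language fluency and time from fracture to surgery are not among the listed DHFA items, so eligibility cannot be applied exactly and the all-patient group will be somewhat broader than the trial population.
- The extract must keep hospital and participation status in anonymised form, and this has to be squared with the consent and data arrangements in section 6.3.
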